### Excluded medications and treatments

To maintain data validity and ensure participant safety, all participants will remain on their prescribed medications as well as any commonly used assistive technologies that will not interfere with measures such as HRV or EEG. Use of medications will be monitored via a self-report assessment at each time point. Some medications may influence HRV, such as anti-hypertensives and anti-depressants. However, β-blockers have been shown to change HRV substantially [66], participants taking β-blockers will be excluded. In a recent study [26], it was concluded that the majority of medications taken by adults with SCI were not associated with any abnormal influences on HRV data. This included cardiac medications such as ace inhibitors, angiotensin II, anti- platelet, calcium channel blockers, muscle relaxants and anti-convulsants. Even though it is expected that these medications will have some influence on HRV measures, randomization should control any such affects. However, if the data suggests that medication usage is not balanced across the RCT arms, then medication usage will be adjusted for in the statistical analysis to limit potential confounding.

### Control of bias

A number of strategies will be used to manage bias. Intention-to-treat analysis involves all randomized participants being included in the statistical analysis according to the group they were originally assigned, regardless of whether they received all or any of the treatment. Intention-to-treat analysis helps to provide an unbiased estimate of the effectiveness of assignment to the HRV-F intervention. Selection bias will be controlled using concealed randomization and multivariable analysis adjusted for potential confounders such as education and age, as well as stratifying for level of lesion and sex. Furthermore, only adults with a chronic SCI will be recruited into the study and inclusion criteria will be strictly adhered to, so as to reduce confounding of data. Performance bias will be minimized by appropriate blinding to group assignment. Attrition bias addressed by using statistical analyses like linear mixed model analysis with repeated measures, as well as regular follow-up/communication with participants in both groups, the length of the assessments will be kept at a minimum, small financial participation incentives will be used and final results of the study will be made available to all participants.

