### Randomization and blinding

RCT participants will be randomized to either the HRV-F group (*N* = 60) or to the no-treatment control group (N = 60) following a stratified randomization procedure. The randomisation allocation ratio is 1:1, while controlling for covariate level of injury (at and above T3 versus below T3). The randomization sequence will be computer generated via RAND function in Microsoft Excel by an independent person and then be uploaded into REDCap. Once the participant is recruited and completed the baseline assessment, then the assessor will inform the team members who are conducting the intervention. The researcher will then randomize a participant via pre-defined randomization sequence in REDCap (see Fig. 1). Team members responsible for recruitment, assessment and analysing the data will be blinded to group allocation. However, the researcher conducting the intervention as well as the participants will be aware of group allocation given it is not possible to blind them to the HRV-F versus control conditions.

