### Power analyses

For the primary outcome measures, assuming an α = 0.05, a small to moderate effect size of 0.3 (based on results from studies in other conditions), with 2 groups (HRV-F and control) of 50 in each group and four assessment periods, estimated statistical power is 0.99 [67]. To allow for reduced participant numbers due to loss to follow-up, sickness, death, or unwillingness to continue, we will recruit up to 120 participants.

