### Statistical methods

Descriptive statistics will be generated for all relevant primary and secondary outcomes at all time-points. Linear mixed models for repeated measures analyses will be used to determine the effectiveness of the HRV-F intervention in autonomic function/HRV and cerebral blood circulation in basal cerebral arteries blood flow. Secondary analyses will determine whether improvements occur in factors such as mental health, cognitive function and sleep associated with the HRV-F intervention. All analyses will be adjusted for factors suspected to confound results, such as education and relevant baseline scores. Latent class mixture modelling will be used to determine trajectories for primary and selected secondary measures like anxiety, depressive mood and quality of life. Missing data will be managed using the linear mixed models, for example, through fitting maximum likelihood estimations generating asymptotically unbiased parameter estimates [68]. Data analyses will be performed using packages such as Statistical Package for the Social Sciences (SPSS version 27, SPSS inc., Chicago, Illinois, USA).

For the implementation study, in which qualitative analyses will also be used, the data will be analysed using valid qualitative packages. Grounded theory, an inductive technique of interpreting the recorded data about the perceptions of the HRV-F and its translation, will be the basis for reaching conclusions about how best to implement and translate the treatment.

For cost-effectiveness, descriptive statistics will be calculated to determine costs and QALYs. The robustness of the costing data will be examined through sensitivity analyses. As in standard economic assessments, costs acquired in this study will likely be skewed, so nonparametric bootstrap methods will potentially be used for testing hypotheses tests and interval estimation. A threshold ICER for Australia will be used to assess value for money.

The ICER will be calculated as per equation (eq. 1) below, that is, the incremental cost per increase in time and frequency domain parameters and as incremental cost per QALY gained in the intervention compared to the controls, in the cost-utility analysis.

1$$ \mathrm{ICER}=\frac{\mathrm{Cost}\ \mathrm{of}\ \mathrm{intervention}\hbox{-} \mathrm{Cost}\ \mathrm{of}\ \mathrm{control}}{\mathrm{Outcome}\ \mathrm{of}\ \mathrm{intervention}\hbox{-} \mathrm{Outcome}\ \mathrm{of}\ \mathrm{control}} $$

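### The article stratifies randomisation by injury level in one section and by level and sex in another, and does not name the randomisation stratum as a model term

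*Protocol article*

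**What the plan says.** Under Randomization and blinding, participants are allocated "following a stratified randomization procedure", at 1:1, "while controlling for covariate level of injury (at and above T3 versus below T3". That is one binary factor, and sex is not mentioned.

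Under Control of bias, the measures against selection bias are concealed randomisation, "multivariable analysis adjusted for potential confounders such as education and age", and then "as well as stratifying for level of lesion and sex".

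Under Statistical methods, the main analysis is set out: "Linear mixed models for repeated measures analyses will be used to determine the effectiveness of the HRV-F intervention". On covariates: "All analyses will be adjusted for factors suspected to confound results, such as education and relevant baseline scores". Neither level of injury nor sex is named there.

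**The concern.** There are two linked problems.

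The first is factual. One section describes two randomisation strata. The other, read as a statement about randomisation, describes four (level by sex). A reader cannot tell which sequence was loaded into REDCap, or whether the allocation does anything about sex.

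The second concerns the model. When allocation is balanced within strata of a prognostic factor, the treatment estimate gains precision, but the reported standard error reflects that gain only if the factor is in the model. The article chooses covariates because they are suspected confounders. A factor balanced by stratification is not expected to confound, so an analyst applying that rule literally could omit it. The reason to include it is that it was used in the randomisation, and the article does not say this. At stake are confidence intervals a little too wide and some lost power.

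**Working it through.** **1. The stated factors side by side**

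| Section | Stratification | Adjustment factors named |
|---|---|---|
| Randomization and blinding | level (T3 and above vs below) | none, though level is called a covariate |
| Control of bias | level and sex | education, age (open list) |
| Statistical methods | none | education, baseline scores (open list) |

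The first two rows disagree on sex. No row names the T3 stratum as a term in the mixed model.

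**2. The plan's own figure**

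The plan gives no figure for this point. Its one design figure is power of 0.99 with 50 per group, effect size 0.3 and four assessments, "assuming an α = 0.05". Taking 0.3 as Cohen's f in a repeated-measures ANOVA, the between-group noncentrality at an assumed within-person correlation of 0.3 is 0.09 × 100 × 4 / (1 + 3 × 0.3) = 18.9, which gives power 0.991. The group-by-time test gives at least 0.9997 at every correlation tried from 0 to 0.8. The figure can therefore be reproduced on that reading, and it does not depend on stratification.

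**3. Cost of leaving the stratum out**

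Inputs: 50 per arm (Power analyses); alpha 0.05, taken as two-sided. Assumptions: strata of 48 and 52, exact 1:1 balance within strata, a true effect of 0.5 residual SD, and a single-time-point linear model standing in for the mixed model. R² is the share of outcome variance, after the other covariates, that the stratum explains. The article gives no value for it, so a range is used.

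- The reported standard error is too large by 1/√(1 − R²).
- Type I error is about 2 × [1 − Φ(1.96/√(1 − R²))]. At R² = 10%, 1.96 × 1.054 = 2.066, which gives 3.9%.

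Simulation, 20,000 replicates per setting:

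| R² | SE ratio | Type I without stratum (formula / simulated) | Power without | Power with | Loss (points) |
|---|---|---|---|---|---|
| 2% | 1.01 | 4.8% / 4.9% | 70.0% | 70.8% | 0.8 |
| 5% | 1.03 | 4.4% / 4.5% | 70.0% | 71.9% | 1.9 |
| 10% | 1.05 | 3.9% / 3.9% | 70.4% | 74.0% | 3.6 |
| 20% | 1.12 | 2.8% / 2.8% | 71.2% | 78.4% | 7.2 |
| 30% | 1.20 | 1.9% / 2.0% | 73.1% | 84.0% | 10.9 |

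With the stratum in the model, simulated type I error was 4.9–5.1% throughout. At R² = 10% under the null, the estimate's true SD was 0.190 under both models, while the mean reported standard error was 0.200 without the stratum and 0.189 with it. The estimate is the same; only its reported precision differs.

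**4. Which rows apply**

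Statistical methods commits to adjusting for baseline scores, which absorbs much of what level explains. Suppose level explains a share S of both baseline and follow-up variance, and the two correlate at r. The share remaining is the squared partial correlation, R² = S(1 − r) / [(1 + r)(1 − S)].

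- r = 0.7 (assumed): S = 10% gives 0.03/1.53 = 2.0%; S = 20% gives 0.06/1.36 = 4.4%; S = 30% gives 0.09/1.19 = 7.6%.
- r = 0.5 (assumed): S = 10% gives 0.05/1.35 = 3.7%; S = 20% gives 0.10/1.20 = 8.3%; S = 30% gives 0.15/1.05 = 14.3%.

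Five of the six cases fall at about 2–10%. The exception pairs the strongest assumed effect of level with the weaker correlation.

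**The case against.** The strongest objection concerns the model term. Both covariate lists are introduced as examples, so the T3 stratum is unnamed, not excluded, and a full list of fixed effects is something a journal article commonly leaves to an analysis plan. This stands. A reader might infer that the trial will analyse without its stratification factor, but the text does not say so. What remains is that the stated selection rule does not bring the factor in.

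Next, the Control of bias phrase follows directly on the adjusted analysis, so it could describe a stratified analysis. On that reading the conflict eases and level would be an analysis factor. The reading is possible, but the sentence is about selection bias and opens with concealed randomisation, so stratified randomisation is the more natural sense. Even on the other reading, Statistical methods names neither factor and the wording needs to be reconciled.

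A reader might also infer a large loss, such as the 7–11 points in the lower rows of the table. That requires level to remain strongly prognostic after baseline adjustment, which the documents do not show. The Background reports reduced low-frequency HRV in both tetraplegia and paraplegia and a task response in high lesions; it does not call level the main determinant of autonomic function.

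Finally, the error is in the safe direction: no bias and no excess of false positives. That stands too. Nor does the article claim that the arms will be balanced on sex; it claims only stratification.

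**Conclusion.** The disagreement over sex is in the text, and an analysis plan that is not shown cannot remove it, because both sections state their factors. It is a documentary inconsistency that should be corrected.

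The model-term part holds as a modest, conditional point. If the stratum is omitted, the treatment estimate stays unbiased, its standard error is about 1–5% too large, two-sided type I error is about 4.9–3.9%, and about 1–4 power points are lost. This rests on level explaining an assumed 2–10% of residual variance after baseline adjustment, an assumed 0.5 SD effect, 50 per arm and exact balance within strata. The loss is greater only if level remains strongly prognostic once baseline is in the model. The point does not threaten the validity of the trial's conclusions.

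**What to change.** - Make Randomization and blinding and Control of bias name the same stratification factors, matching the sequence actually generated.
- State in Statistical methods that the factors used in the randomisation enter every primary and secondary mixed model as fixed effects, whether or not they are suspected confounders.
- If sex was not a stratification factor, delete the words *and sex* from Control of bias, or pre-specify sex as a covariate and describe it as such.

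The cost is one corrected phrase, one model line and one degree of freedom for level, or two if sex is included. No change to sample size, assessments or data collection is needed.

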### Adverse events

HRV-F is a low risk self-regulation intervention. It is unlikely to result in adverse events caused by the intervention or the devices used in the study. To monitor possible adverse events the following will occur: (a) A detailed record of all related and unrelated adverse events will be documented and kept in a locked cabinet or online in a password protected file. (b) The impact of each event on participant safety or on trial conduct will be clarified. (c) Assess and categorise the safety reports received from investigators. (d) Report all suspected unexpected serious adverse reactions. (v) Report to the sponsor (The University of Sydney) within 24-h of becoming aware of any serious adverse events. (vi) Report to the sponsor all safety critical events and any additional requested information relating to reported deaths.

### Power analyses

For the primary outcome measures, assuming an α = 0.05, a small to moderate effect size of 0.3 (based on results from studies in other conditions), with 2 groups (HRV-F and control) of 50 in each group and four assessment periods, estimated statistical power is 0.99 [67]. To allow for reduced participant numbers due to loss to follow-up, sickness, death, or unwillingness to continue, we will recruit up to 120 participants.

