### Primary physiological outcome measures

Electrocardiography (ECG) assessment from which HRV will be calculated at 10 weeks (short-term effect), in order to determine whether HRV-F results in improved autonomic nervous system function. HRV via ECG (electrodes on chest, modified lead II configuration) will be measured using the PowerLab 8/35 8-channel, 16-bit resolution recorder data acquisition system with programmable gain and two galvanically-isolated channels FE232 Dual Bio Amps (ADInstruments, www.adinstruments.com). A sampling rate of 512 Hz will be used for time/spectral analyses [4]. HRV signal processing will be performed using Kubios HRV Premium software (Version 3.3.1, University of Kuopio, Finland). HRV indexes neuro-cardiac function/regulation, generated by bidirectional heart-brain interactions (i.e., top-down influences on cardiac and peripheral physiological processes and bottom-up influences on central control mechanisms) and dynamic non-linear autonomic nervous system (ANS) regulation. HRV reflects the innervation of the heart by the sympathetic/parasympathetic divisions of the ANS [4]. In the time domain, average and standard deviation of the normal-to-normal intervals (SDNN; the variability of the heart) and root mean square of the successive differences (RMSSD, vagally mediated HRV) will be calculated. In the frequency domain, low frequency (LF), high frequency (HF, cardiac vagal control) and total power will be assessed. Details of a HRV protocol we have employed are available [40].
(ii)Functional transcranial doppler sonography (fTCD) to assess cerebral artery blood flow at 10 weeks (short-term effect), to determine cerebrovascular benefits associated with the HRV-F, using Multi-Dop T digital with QL routine software (Compumedics Limited, www.compumedics.com.au). fTCD assesses real-time cerebral blood flow velocities/circulation in basal cerebral arteries of the participants in response to the intervention [41]. fTCD is a reliable method for measuring cerebrovascular changes, provides high temporal resolution and is least susceptible to artefact than other imaging techniques [41].

Electrocardiography (ECG) assessment and Functional transcranial doppler sonography will be performed using the same instruments (as per primary outcomes) at 6 and 12 months (long-term effects).

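### The 0.99 power given for the primary outcomes is computed on four visits, but the primary outcomes are set at 10 weeks; power there depends on the unstated metric of the effect size 0.3

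*Protocol article*

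**What the plan says.** The Power analyses section opens with "For the primary outcome measures" and then gives its inputs, "assuming an α = 0.05" and "a small to moderate effect size of 0.3 (based on results from studies in other conditions"), followed by the design and the result: "with 2 groups (HRV-F and control) of 50 in each group and four assessment periods, estimated statistical power is 0.99". Recruitment is raised to as many as 120 to cover losses. The section does not say whether 0.3 is a standardised mean difference (d) or Cohen's f, and it gives no within-person correlation.

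The section Primary physiological outcome measures ties the primary outcomes to one time point: "Electrocardiography (ECG) assessment from which HRV will be calculated at 10 weeks (short-term effect"), with the same time point for transcranial Doppler. The later recordings are described separately: ECG and Doppler "will be performed using the same instruments (as per primary outcomes) at 6 and 12 months (long-term effects"). Table 1 agrees. The primary rows are ticked at day 0 and week 10 only, and long-term HRV and Doppler stand under the secondary outcomes.

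Statistical methods plans linear mixed models for repeated measures, adjusted for relevant baseline scores among other factors.

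**The concern.** The power figure is attached to the primary outcomes but counts four occasions. Two of them, 6 and 12 months, do not belong to the primary outcomes as defined. The document gives no power for the comparison that decides the primary question, HRV-F against control at 10 weeks.

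The effect size adds a second difficulty. Called small to moderate, 0.3 reads most naturally as a difference of 0.3 SD, since the usual benchmarks for d are 0.2 and 0.5. On the scale of f the benchmarks are 0.1 and 0.25, so 0.3 would already exceed medium, and with two groups it equals a difference of 0.6 SD. The two readings lead to very different power at 10 weeks.

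What is at stake is how the result is read. A reader who takes the sentence at face value believes the trial is almost certain to detect a small-to-moderate effect on its primary outcomes, and would weigh a null result accordingly.

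**Working it through.** **Inputs.** From Power analyses: 50 per arm (N = 100), k = 2 groups, m = 4 occasions, α = 0.05, effect size 0.3, power 0.99. From the outcome section and Table 1: primary time point 10 weeks. Assumed, because the document does not give them: a two-sided test, a baseline-to-10-week correlation r from 0 to 0.8, and a within-person correlation ρ for the four-visit formulas.

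**1. Reproducing 0.99.** Three four-occasion repeated-measures F calculations arrive at it.

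- Group-by-time interaction, f = 0.3, λ = N(m−1)f² = 100 × 3 × 0.09 = 27, df 3 and 294: power 0.996.
- Between-groups effect, f = 0.3, ρ = 0.3, λ = Nmf²/(1+(m−1)ρ) = 36/1.9 = 18.9, df 1 and 98: power 0.991. At ρ = 0.5 it is 0.964.
- Interaction with d = 0.3 converted to f = 0.15, λ = Nmf²/(1−ρ) = 9/(1−ρ), df 3 and 294: 0.957 at ρ = 0.5, 0.986 at ρ = 0.6 and 0.990 at ρ = 0.62.

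So the number can be obtained from the stated inputs, but each route is a four-visit test.

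**2. Power at 10 weeks.** For a standardised difference d with n per arm, the noncentrality of the t test is d/√(1−r²) × √(n/2). With n = 50, √(n/2) = 5. Degrees of freedom are 98 unadjusted and 97 with the baseline covariate.

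| r (assumed) | d = 0.3: noncentrality | d = 0.3: power | d = 0.6 (f = 0.3): noncentrality | d = 0.6: power |
|---|---|---|---|---|
| 0 (unadjusted) | 1.50 | 0.32 | 3.00 | 0.84 |
| 0.5 | 1.73 | 0.40 | 3.46 | 0.93 |
| 0.7 | 2.10 | 0.55 | 4.20 | 0.99 (0.986) |
| 0.8 | 2.50 | 0.70 | 5.00 | above 0.99 |

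If all 60 per arm were retained, d = 0.3 would give 0.37 unadjusted and 0.63 at r = 0.7. Reaching 0.99 for d = 0.3 with 50 per arm would need r of about 0.94. Unadjusted, it would need about 410 per arm.

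**3. Does f = 0.15 over four visits amount to 0.3 SD between arms?** No. Take a difference of 0 at baseline and 0.3 SD at each of the three follow-ups. The mean is 0.225, and the squared deviations sum to 0.225² + 3 × 0.075² = 0.0675. The interaction then has λ = (50/2) × 0.0675/(1−ρ), which is 3.375 at ρ = 0.5 and 5.625 at ρ = 0.7. Power is 0.30 and 0.48. The 0.986 in the third route belongs to a larger pattern of effects than that.

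**4. Detectable difference at 80% power, 10 weeks, 50 per arm.** 0.57 SD unadjusted, 0.49 SD at r = 0.5, 0.40 SD at r = 0.7.

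**The case against.** The strongest reply is that four occasions match the planned analysis. The mixed model uses repeated measures, and HRV and Doppler are recorded at all four visits. That is true of the model. It does not move the primary outcome from 10 weeks to the whole follow-up, and the power sentence is about the primary outcomes.

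A second reply is that the structure of the calculation (groups, occasions and a reproducible 0.99) points to Cohen's f. On that reading 10-week power is 0.84 to 0.99 for r from 0 to 0.7, and because baseline adjustment is planned the adjusted figures are the relevant ones. This stands as a possibility. The correction would then be modest, but the stated size of 0.3 would mean a difference of 0.6 SD, which the label does not convey.

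A third reply is that the metric and correlation may be given in the full protocol or analysis plan. Their absence from an article is not the point here. The printed figure conflicts with the article's own definition of the outcomes to which it is attached.

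Three stronger conclusions are tempting and go too far:

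- A reader might infer that 0.99 is an arithmetic slip. It is not, since it follows from the stated inputs by standard four-visit formulas.
- A reader might infer that it can arise only with f = 0.3. The f = 0.15 route at ρ of about 0.6 shows otherwise.
- A reader might infer that the trial is underpowered, or more likely than not to miss its target effect. That requires 0.3 to be d, which the document does not say. Even then power passes one half at r = 0.7.

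**Conclusion.** The point holds as a mismatch between the power statement and the definition of the primary outcomes. The 0.99 is a four-visit figure and is not the power for a 0.3 SD difference between arms at 10 weeks, whichever route produced it.

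The size of the gap depends on the metric. If 0.3 is d, the better fit to the label, power is 0.32 unadjusted and 0.40 to 0.70 for r = 0.5 to 0.8, far below 0.99. If 0.3 is f, it is 0.84, 0.93 and 0.99 at r = 0, 0.5 and 0.7, so the gap is small or absent.

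These figures assume 50 evaluable per arm, a two-sided test at the full 0.05 for a single measure, and correlations that the document does not give. The document does not settle which metric was meant, so neither set can be called the trial's power. The mismatch itself does not depend on these assumptions.

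**What to change.** Keep the sample size. Replace the power sentence with the power, or the detectable difference, for the 10-week between-arm contrast from the mixed model. Say whether the effect size is d or f, and state the assumed baseline-to-10-week correlation with its basis. A suitable form would be: with 50 evaluable participants per arm and two-sided α of 0.05, the trial has 80% power for a standardised 10-week difference of 0.57 unadjusted, 0.49 at a baseline correlation of 0.5, or 0.40 at 0.7. If a four-visit calculation is kept, label it as supporting the longitudinal analysis rather than the primary outcomes.

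This rewords one paragraph and adds no participants, visits or analyses. The only cost is a less favourable stated figure.
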